**Methods/design:**

A five-arm, parallel, single-blinded, randomized, sham-controlled trial was designed. Patients with CNP of more than 3 months’ duration are being recruited from Guangdong Provincial Hospital of Chinese Medicine (China). Following examination, 175 patients will be randomized into one of five groups (35 patients in each group) as follows: a traditional acupuncture group (group A), a shallow-puncture group (group B), a non-acupoint acupuncture group (group C), a non-acupoint shallow-puncture group (group D) and a sham-puncture group (group E). The interventions will last for 20 min and will be carried out twice a week for 5 weeks. The primary outcome will be evaluated by changes in the Northwick Park Neck Pain Questionnaire (NPQ). Secondary outcomes will be measured by the pain threshold, the Short Form McGill Pain Questionnaire-2 (SF-MPQ-2), the 36-Item Short-Form Health Survey (SF-36) and diary entries. Analysis of the data will be performed at baseline, at the end of the intervention and at 3 months’ follow-up. The safety of acupuncture will be evaluated at each treatment period.

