#### Sample size calculation

Following an academic literature review, a pilot study on acupuncture and its analgesic effect in CNP was identified [26]. The NPQ will be used as the primary outcome measure in assessment of the analgesic effect of acupuncture in this trial. Results from the pilot study with a two-arm design showed that the mean changes in NPQ were 20.71 ± 11.91 (acupuncture group) and 24.04 ± 11.83 (control group) [26]. However, our trial is a five-arm parallel-group study with the aim of assessing the efficacy of acupuncture. The mean ± standard deviation (SD) values reported in the pilot study will be used as the expected values in the treatment group and four control groups in the present study. PEMS 3.1 software was used to perform the sample size calculation. Thus, we calculated the appropriate trial sample size with 90% power, and the significance level was 0.05. The results showed that a clinically important difference was detected using a minimum sample size of 30 individuals in each group. With a maximum allowable dropout rate of 15%, a total of 175 subjects (35 per group) are being recruited.

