#### Statistical analysis

A statistical analysis will be performed using the Statistical Package for Social Sciences (SPSS, version 16.0, SPSS Inc., Chicago, IL, USA) in the Center of Acupuncture Clinical Research. A full analysis set (FAS) will be performed as the main analysis. According to the principle of intention-to-treat (ITT), any participants who randomly receive at least one treatment should be included in the main analysis dataset. The per-protocol (PP) set as the subset of FAS will include subjects who complete the study and have main variable baseline values in this trial. To be included in the safety set, patients will receive at least one safety evaluation after treatment. Statistical analysis of the main parameters will be carried out at baseline, at each visit and in the follow-up period. Frequency tables and charts will be used to analyze completed AE questionnaires.

Descriptive statistics will be performed to compare baseline information, patient characteristics and an evaluation of the credibility of the five groups. To determine the primary and secondary outcomes, the mean differences from baseline to the end of follow-up period will be compared and analyzed. Group differences for continuous variables will be analyzed using analysis of variance (ANOVA) to compare the subjective and semi-objective outcomes. The Wilcoxon rank sum test will be used to compare the outcome measurements before and after treatment. The differences in categorical variables between groups and adverse effects will be analyzed using the chi-square test. A *P* value of 0.05 or less will be considered significant.

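### Comparing NPQ change by ANOVA without baseline NPQ as a covariate is valid, but it gives up about 10% to 35% of the variance that ANCOVA would remove

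*Protocol article*

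**What the plan says.** The Abstract defines the primary outcome through changes in the NPQ. The Statistical analysis section fixes the quantity to be compared: "the mean differences from baseline to the end of follow-up period will be compared and analyzed". It also fixes the test: "Group differences for continuous variables will be analyzed using analysis of variance (ANOVA) to compare the subjective and semi-objective outcomes". No covariate is named there or elsewhere in the article.

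Baseline data have a descriptive role only: "Descriptive statistics will be performed to compare baseline information, patient characteristics and an evaluation of the credibility of the five groups". Randomization uses blocks of five, and no stratification on baseline NPQ is described.

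A baseline NPQ is nevertheless expected. The same section states "Statistical analysis of the main parameters will be carried out at baseline, at each visit and in the follow-up period", and its per-protocol definition requires baseline values of the main variable. The Primary outcome section mentions completion only after each treatment and in follow-up, but no change can be calculated without a baseline score.

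**The concern.** Subtracting the baseline is the same as adjusting for it with a slope fixed at 1. With equal variances at baseline and at the end, the slope of final score on baseline equals the correlation r, which is below 1. Subtraction therefore over-corrects: an arm that starts worse by chance tends to show a larger improvement whatever its treatment. ANCOVA estimates the slope from the same data and removes that part of the error.

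What is at stake is the width of the confidence intervals for the comparisons with the traditional acupuncture arm, and how far each one depends on a chance difference at baseline. With about 35 patients per arm, the loss is worth avoiding when the remedy needs no new data.

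**Working it through.** **Inputs from the Sample size calculation section.** Mean NPQ changes are 20.71 (SD 11.91) and 24.04 (SD 11.83), and these "will be used as the expected values in the treatment group and four control groups in the present study". The section states 30 per group before dropout, 35 per group recruited, 90% power and a significance level of 0.05.

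- Planning difference: 24.04 − 20.71 = 3.33.
- Pooled SD of change: √[(11.91² + 11.83²)/2] = 11.87.

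**The plan's own figure.** For a two-sided pairwise comparison at 90% power, n per group = 2 × (1.960 + 1.282)² × (11.87/3.33)² ≈ 267.02, rounded up to 268. The stated 30 is not reproduced. At 30 per group the power is about 19%. At 35 the standard error is 11.87 × √(2/35) = 2.84, and the power is Φ(3.33/2.84 − 1.96) ≈ 22%. This is a separate matter and serves here only as the reference point.

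**Precision.** Let s be the common SD of baseline and final NPQ, and r their correlation. The article gives no r, so a range is assumed.

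- Variance of the change: 2s²(1 − r).
- Residual variance under ANCOVA: s²(1 − r²).
- Ratio, ANCOVA to change: (1 + r)/2.

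**Baseline difference left in the change score.** An SD of change of 11.87 implies s = 11.87/√[2(1 − r)]. The SD of the chance baseline difference between two arms of 35 is s√(2/35). The change score keeps (1 − r) of it, so the retained error has SD 11.87 × √[(1 − r)/35].

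| Assumed r | Variance ratio | 35 per arm acts like | Implied baseline SD | SD of baseline difference | SD of retained error | Retained SD / 3.33 | Pairwise power at 35 |
|---|---|---|---|---|---|---|---|
| 0.3 | 0.65 | 54 | 10.03 | 2.40 | 1.68 | 50% | 31% |
| 0.5 | 0.75 | 47 | 11.87 | 2.84 | 1.42 | 43% | 27% |
| 0.7 | 0.85 | 41 | 15.32 | 3.66 | 1.10 | 33% | 25% |
| 0.8 | 0.90 | 39 | 18.77 | 4.49 | 0.90 | 27% | 23.5% |

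The power column uses the ANCOVA variance and takes all 35 patients per arm as analysed. Without adjustment it is about 22%. At 30 per arm, power goes from 19% to 27%, 24%, 22% and 21%.

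**The two descriptions are one loss.** At r = 0.5 the change-score contrast has variance 2.84² ≈ 8.05 and the ANCOVA contrast 0.75 × 8.05 ≈ 6.04. The gap of 2.01 equals 1.42², the variance of the retained baseline error. The imbalance is already inside the change-score standard error and must not be counted again.

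**Simulation check.** At r = 0.5 and 30 per arm, 4,000 simulated two-arm comparisons gave power of 18.9% for the change score and 22.6% for ANCOVA. The normal-approximation formula gives 19% and 24%.

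**The case against.** The strongest reply is that nothing here is invalid. In a randomised trial, ANOVA on change is unbiased and keeps its type I error rate. The pilot figures are also mean changes, so planning and analysis are on the same scale. That stands: the fault is lost precision, with bias only conditional on an observed baseline difference.

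A second reply is that a condensed article may leave covariates to an analysis plan that is not shown. This stands only in part. The article does not leave the method open: it names the compared quantity and the test, and it gives baseline data a descriptive use.

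A third reply concerns the promised gain. A reader might infer that ANCOVA can never have a larger variance than the change score. With five arms sharing one pooled slope, that can fail for a pairwise contrast. Suppose two arms have slope 0.9 and the other three 0.3. The pooled slope is (2 × 0.9 + 3 × 0.3)/5 = 0.54. In units of s², and ignoring error in the estimated slope, the contrast between the first two arms has per-patient variance (1 − 0.81) + (0.9 − 0.54)² = 0.32 under ANCOVA. For the change score it is 2(1 − 0.9) = 0.20. The example is extreme, but it shows that the advantage rests on slopes being similar across arms.

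Finally, the size for the secondary outcomes cannot be stated. The article gives no variances for them, and the SF-MPQ-2 section sets out no visit schedule.

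**Conclusion.** The point holds as one of efficiency. With equal variances, a common slope and r between 0.3 and 0.8, adding baseline NPQ to the model cuts the variance of each arm contrast by 10% to 35%. The same loss, seen as retained baseline error, has an SD of about 0.9 to 1.7 NPQ points at 35 per arm, or roughly 27% to 50% of the 3.33-point planning difference. The gain shrinks as r approaches 1.

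Two stronger readings are tempting and are not supported.

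- A reader might set the SD of the chance baseline difference itself (2.84 points at r = 0.5) against 3.33 and conclude that imbalance could produce the whole planned effect. The change score carries only the (1 − r) share, which is 1.42 points at that r, and its standard error already allows for it.
- A reader might expect the adjustment to rescue an underpowered trial. On the article's own inputs, pairwise power at 35 per arm stays between about 23.5% and 31%, against a stated 90%. The sample-size shortfall is a larger and separate problem. It neither proves this point nor is solved by it.

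**What to change.** Name ANCOVA as the primary analysis, with arm as factor and baseline NPQ as covariate, or use a repeated-measures model with the same baseline adjustment. Report adjusted mean differences with 95% confidence intervals for the prespecified arm contrasts. Apply the same model to continuous secondary outcomes that have a baseline value. Check the common slope with an arm-by-baseline term, and state in advance what will be done if slopes clearly differ. Fix all of this before unblinding, so that adjustment cannot be chosen after an imbalance is seen.

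The cost is a sentence or two in the Statistical analysis section, one error degree of freedom (169 instead of 170 if all 175 patients are analysed) and the common-slope assumption. No new data are needed. The sample-size justification has to be corrected on its own account.

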**Discussion:**

The purpose of this trial is to determine whether traditional acupuncture is more effective for chronic pain relief than sham acupuncture in adults with CNP, and to determine which type of sham acupuncture is the optimal control for clinical trials.

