In view of these doubts, the influence of different needling points and depths should be investigated. First, the acupoints of local lesions including *Jingbailao* (EX-HN 15) and *Jianzhongshu* (SI 15) are commonly used in our hospital for neck pain [15]. The analgesic mechanism of acupoints on local lesions has been established in the spinal segments control theory to explain the gate control theory [16, 17]. According to the innervations of the pain focus, the effects of stimulation of EX-HN 15 and SI 15 on neck analgesia will be studied for feasibility and repeatability [15]. Second, several different groups of non-acupoints and shallow punctures will be established to determine whether traditional acupuncture is more effective for chronic pain relief than sham acupuncture in adults with CNP. The different depth and placement of needle insertion will also be investigated to determine efficacy [18]. Third, a single-blinded practice will be used and the adequacy of subject blinding will also be carefully assessed. The patients will be advised to lie in the prone position on the treatment couch and will be unaware of the treatment course in this trial. Data collection will be completed by the researchers over a 3-month follow-up period. Finally, we will assess the pain threshold (PT) and pain diary as semi-objective outcomes to avoid subjective results.

In this research, a randomized clinical trial will be performed to determine whether the outcome of traditional acupuncture treatment is significantly different to sham acupuncture in relieving CNP. We also aim to investigate which type of sham acupuncture is the optimal control for clinical trials.

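### The only between-group test stated for continuous outcomes is a five-group ANOVA at 0.05, with no A-versus-sham contrast and no single analysis time, so a significant result need not support the trial's main claim

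*Protocol article*

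**What the plan says.** **Questions.** The abstract's Discussion gives the main purpose as "to determine whether traditional acupuncture is more effective for chronic pain relief than sham acupuncture in adults with CNP". A second aim, stated there and again in the Background, concerns the choice of sham: "We also aim to investigate which type of sham acupuncture is the optimal control for clinical trials". The Background adds a third: "The different depth and placement of needle insertion will also be investigated to determine efficacy". The main Discussion closes by asking whether acupuncture is more effective than a placebo.

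**Test.** Statistical analysis says: "Group differences for continuous variables will be analyzed using analysis of variance (ANOVA) to compare the subjective and semi-objective outcomes". It names no contrast or pairwise comparison. The Wilcoxon test there is for before/after comparison and the chi-square test for categorical variables, so neither compares A with sham on a continuous outcome. The threshold is a P "value of 0.05 or less will be considered significant".

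**Analysis times.** The same section says "Statistical analysis of the main parameters will be carried out at baseline, at each visit and in the follow-up period". It then says that, for the primary and secondary outcomes, mean differences from baseline to the end of follow-up will be compared. The abstract's Methods/design says "Analysis of the data will be performed at baseline, at the end of the intervention"; its list of times ends with the 3-month assessment.

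**The concern.** A one-way ANOVA across five arms tests whether all five means are equal. The aims are narrower: A against sham or placebo, and sham against sham. The overall test can be significant because one sham differs from the rest, it has no direction, and it does not say which arms differ. If it is the decision test, a positive primary analysis may say little about traditional acupuncture.

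The aims can then be reached only through further comparisons, which this text does not define. How far their error is controlled depends on how they are run. The choice of analysis time is also open, because three descriptions are given and one threshold covers them all. Finally, no result is tied to calling a sham the optimal control, so a non-significant sham-versus-sham difference could be taken as equivalence.

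**Working it through.** **Inputs.** Five arms with equal allocation (Randomization and allocation concealment). Minimum 30 per group, alpha 0.05, 90% power, and pilot NPQ changes of 20.71 (SD 11.91) and 24.04 (SD 11.83), with one planning value for all four controls (Sample size calculation). The shifts of 5 and 10 points are assumptions.

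1. Difference = 24.04 − 20.71 = 3.33. Pooled SD = √((11.91² + 11.83²)/2) = 11.87. Only the size of the difference is used here, not its direction.

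2. The plan's own figure. A two-sided two-sample comparison at 90% power needs n = 2 × (11.87 × (1.960 + 1.282)/3.33)² ≈ 267, so 268 per group, not 30. That is a separate problem, and this point does not depend on it; 30 per arm is used below because it is the plan's minimum.

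3. Overall ANOVA when only E is shifted by D and A = B = C = D. The noncentrality is λ = n × Σ(mean − grand mean)²/SD² = 30 × 0.8 × D²/11.87². The critical F on 4 and 145 degrees of freedom is 2.43. λ depends only on D², so the rejection rate is the same if E is better or worse than the rest. It is also the same if the one shifted arm is B, C or D, in which case A equals E as well.

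4. Unadjusted pairwise t tests at 0.05 (pooled variance), run only after a significant ANOVA. By simulation, the probability of at least one false difference among the six pairs of A, B, C and D is in the last column.

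| Shift in E (points) | λ | ANOVA significant | False difference among A to D after a significant ANOVA |
|---|---|---|---|
| 3.33 (plan's own difference) | 1.89 | 16% | 9% |
| 5 (assumed) | 4.26 | 33% | 13% |
| 10 (assumed) | 17.03 | 92% | 20% |

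5. All five means equal, by simulation:

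| Unadjusted tests at 0.05 | Without a significant ANOVA first | Only after a significant ANOVA |
|---|---|---|
| Four A-v-control tests | 15% | 4% |
| All ten pairs | 28% | 5% |

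6. Power at the planning values, 30 per arm, two-sided 0.05:
   - A v E: SE = 11.87 × √(2/30) = 3.06; 3.33/3.06 = 1.09; power about 19%.
   - A v the mean of the four controls: SE = 11.87 × √(1/30 + 1/120) = 2.42; 3.33/2.42 = 1.37; power about 28%.
   - Overall ANOVA: λ = 1.89; power 16%.

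7. Analysis times side by side. Statistical analysis has both every visit and the single interval from baseline to the end of follow-up. The abstract has the end of the intervention and 3 months. The NPQ is completed after each treatment and in follow-up (Primary outcome measurement). None of these is marked as the primary time.

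**The case against.** **A protocol article may leave post hoc tests and multiplicity to a full protocol or analysis plan.** This stands in part. Silence on adjustment does not show that none is planned, and no follow-on tests are named here, adjusted or not. But the article does commit to a test, a threshold and several analysis times, and the test as worded does not address the stated aims.

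**ANOVA can include planned contrasts or a factorial layout.** This stands. The text does not exclude them, so it goes too far to say the method cannot answer the questions. What can be said is that no contrast is named.

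**The error rates depend on the scenario.** This stands. A reader might infer that follow-on comparisons carry a 15% or 28% false-positive rate. Those rates apply only to tests run without the ANOVA as a gate; with the gate and all means equal, the error is about 5%. Inflation after the gate appears when some means differ and others do not, and its size depends on the assumed shift. The 92% and 20% figures need a shift three times the plan's own difference.

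**The ANOVA may not be repeated at every visit.** A reader might infer such a repetition at 0.05. The sentence on visits names no test, and the sentence just before the ANOVA names one interval. The documents support a conflict over timing, not a count of repeated tests.

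**A v E is not the only possible primary contrast.** This stands. The article itself reports that about 40%, or nearly half, of subjects could tell this type of needle from real acupuncture, and the sample size section treats all four arms as controls. A v E is suggested because the Discussion asks about a placebo and Table 1 describes E's needle as one.

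**Conclusion.** The concern holds in this limited form. The stated between-group analysis names no comparison of A with sham, and the analysis times are not reconciled. If the overall ANOVA is the decision test, it can be significant when A equals three of its four shams: in 16% of trials at the plan's own 3.33-point difference, and in 33% and 92% at assumed shifts of 5 and 10 points. Unadjusted pairwise tests after it would then give a false difference among A to D in 9%, 13% and 20%.

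These figures assume 30 analysed per arm, a common SD of 11.87, normal data and one shifted arm. The pairwise figures also assume that such tests are run unadjusted at 0.05, which the article does not say. The documents do not support the stronger conclusions that the error rate is several times nominal in general, or that an ANOVA could never address the aims.

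**What to change.** Before unblinding, amend the analysis wording as follows.

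- **Time point.** Name one primary NPQ time point and make all others secondary. Statistical analysis already gives the end of follow-up. Bring the abstract and both sentences of that section into line.
- **Primary contrast.** Replace the overall ANOVA as the decision test with one prespecified contrast that matches the stated question, such as A v E at two-sided 0.05. If it is significant, test A v B, C and D with Holm (first step 0.05/3 = 0.0167) or Dunnett.
- **Power.** State that at the planning values and 30 per arm A v E has about 19% power, against 28% for A v the mean of the four controls and 16% for the overall ANOVA. The change makes the result interpretable; it does not make the trial adequately powered.
- **Choice of sham.** Report sham-versus-sham differences as estimates with 95% confidence intervals. State that no sham will be called optimal or equivalent because a difference is not significant.
- **Depth and location.** Add a secondary 2 × 2 analysis of A to D only after the description of group C is reconciled: the Interventions text says non-acupoint needles are inserted without acupuncture techniques, while Table 1 requires de-qi in that group.

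The cost is wording only, with no new data. The small downside is that the individual A v B, C and D tests become stricter.

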#### Secondary outcome measurement

##### Pain threshold

A patient’s pain threshold (PT) is a semi-objective outcome and will be measured twice after each treatment. The PT measuring device (EP601C, East China Normal University of Science and Technology, Guangxi, China) has a 5-mA range. The positive electrode (anode) of the device is placed in the area of pain, and the other electrode is placed on the leg. According to the staircase method, the stimulus selection procedure with an increasing sequence of current stimulation from 0 mA in 2-mA steps will be presented to the patient. The patient will control the switch and press the stop key once they feel pain. The current strength (mA) on the screen will be recorded and the sequence direction will then be reversed. The descending sequence will be stopped when the participant feels pain, and the sequence points will be reversed again [23]. Three measurements will be recorded and the average PT calculated for each patient. PT will be assessed before and after treatment and the mean value calculated after the 5th and 10th treatments.

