##### Short-form 36-Item Health Survey (SF-36)

Health status will be evaluated using the Chinese version of the Medical Outcome Study Short-form 36-Item Health Survey (SF-36). The SF-36 will be used to test the correlation between health-related quality of life and related factors (sex, age, physical function and daily functioning) rated on a 5-point scale [25]. This survey will be performed before treatment, after the 5th and 10th treatments and at the end of the follow-up period.

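### The plan names an independent-samples test (Wilcoxon rank sum) for before-after measurements that are paired within patient; a paired test should be named

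*Protocol article*

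**What the plan says.** The Statistical analysis section separates two kinds of comparison. Between arms, the plan is: "Group differences for continuous variables will be analyzed using analysis of variance (ANOVA) to compare the subjective and semi-objective outcomes". The quantity is change from baseline: "the mean differences from baseline to the end of follow-up period will be compared and analyzed". For change within patients, it adds: "The Wilcoxon rank sum test will be used to compare the outcome measurements before and after treatment". One threshold is given for all tests: a P "value of 0.05 or less will be considered significant".

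The outcome sections show that the before and after values belong to the same people. For the pain threshold: "PT will be assessed before and after treatment and the mean value calculated after the 5th and 10th treatments". For the SF-36: "This survey will be performed before treatment, after the 5th and 10th treatments and at the end of the follow-up period". The Sample size calculation section describes the design: "our trial is a five-arm parallel-group study with the aim of assessing the efficacy of acupuncture". So each patient is in one arm only and supplies both a baseline and later values.

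**The concern.** The rank sum (Mann-Whitney) test takes its null variance from two samples of different, unrelated subjects. A patient's score before treatment and the same patient's score afterwards are not unrelated. When they are positively correlated, the difference between the two sets of scores varies less than the test supposes. Its p-values are then too large, so a real within-arm change can be reported as non-significant. The signed-rank test works on each patient's own difference and does not have this fault.

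This is not a detail left to a later analysis plan. A specific test is named for a specific comparison, and it does not fit the data.

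**Working it through.** **1. Can the sentence mean something else?** The sentence just before it gives group differences in continuous outcomes to ANOVA, so this one is not the between-arm analysis. A two-sample test would not cover five arms in any case. The sentence itself says that the comparison is before versus after treatment. The data are therefore paired, and the article names no signed-rank or other paired test.

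**2. Inputs.** From the article: significance level 0.05 (sidedness not stated, two-sided assumed); 35 patients per arm recruited and 30 as the minimum. Assumed: normal scores with equal SD before and after; within-patient correlation ρ between 0 and 0.8, because the article gives none; an illustrative true shift of 0.5 SD, which is not a figure from the article. The article states no operating figure for the before-after test, so there is none to reproduce.

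**3. Why the direction is conservative.** With common SD σ and n pairs, the difference in means has variance 2σ²(1 − ρ)/n. An independent-samples test supposes 2σ²/n. The test statistic is therefore too small by a factor of about √(1 − ρ). At ρ = 0.5 that factor is √0.5 = 0.71.

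**4. Size by simulation.** 20,000 simulated data sets per setting, bivariate normal pairs, n = 35, two-sided 0.05, normal approximation for both tests:

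| ρ | Type I error, rank sum | Type I error, signed-rank | Power at 0.5 SD, rank sum | Power at 0.5 SD, signed-rank |
|---|---|---|---|---|
| 0 | 0.048 | 0.047 | 0.52 | 0.52 |
| 0.3 | 0.022 | 0.050 | 0.52 | 0.66 |
| 0.5 | 0.008 | 0.049 | 0.52 | 0.81 |
| 0.7 | 0.001 | 0.052 | 0.54 | 0.95 |
| 0.8 | 0.0001 | 0.049 | 0.56 | 0.99 |

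At n = 30 the pattern is the same. For ρ = 0.5 the type I error is 0.008 against 0.052, and the power is 0.45 against 0.73. The rank sum test is calibrated only at ρ = 0, which is implausible for repeated scores on one patient.

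**5. Does it matter for the primary outcome at the planned effect?** The Sample size calculation section gives mean NPQ changes of 20.71 (SD 11.91) and 24.04 (SD 11.83) and uses them as expected values for all five arms. Read these as the within-patient change and its SD. With equal SDs before and after, the SD of the change is σ√(2(1 − ρ)). The smaller change, in units of σ, is then (20.71/11.91) × √(2(1 − ρ)) = 1.739 × √(2(1 − ρ)):

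- ρ = 0.3: 1.739 × 1.183 = 2.06
- ρ = 0.5: 1.739 × 1.000 = 1.74
- ρ = 0.7: 1.739 × 0.775 = 1.35
- ρ = 0.8: 1.739 × 0.632 = 1.10

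In 20,000 simulated data sets per setting, the rank sum test rejected in at least 99.99% at each of these correlations, at n = 30 and at n = 35. At changes of that size the wrong test gives the same answer as the right one.

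**The case against.** The strongest reply is that the sentence hardly matters. The trial asks whether traditional acupuncture differs from sham, which is a between-arm question. That question goes to ANOVA on change from baseline, which already uses each patient's own pairing. The error is conservative, and the NPQ changes expected at planning would be found with either test. The sentence may also be a slip for the signed-rank test, in which case no p-value would be affected. All of this limits the consequence. It does not make the wording right: a reader who follows the text will run the wrong test, and the secondary outcomes have no stated effect size that would make them safe.

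Three stronger readings are tempting, and the article does not support them.

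- **Arms could be falsely declared improved.** With positive correlation the opposite holds: false positives are rarer than the nominal 5%.
- **Every within-patient p-value will be wrong.** That requires literal execution and a non-zero correlation. The article gives no correlation and cannot show whether the name is a slip.
- **Efficacy will be claimed from within-arm change, confounded by regression to the mean because entry requires a VAS of 3 or more.** The Statistical analysis section nowhere rests efficacy on the before-after tests; it assigns group differences separately.

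**Conclusion.** The stated test is wrong for the stated comparison, and the severity is modest. With 35 patients per arm and an assumed correlation of 0.3 to 0.7, literal use lowers the true type I error from 0.05 to between about 0.022 and 0.001. At a 0.5 SD shift it gives up about 14 to 41 percentage points of power (0.66 − 0.52 = 0.14; 0.95 − 0.54 = 0.41). These sizes rest on the assumed correlation, normal scores, two-sided testing and a shift chosen for illustration. The practical risk is that smaller within-arm changes are missed, mainly on secondary outcomes. The between-arm ANOVA, and the trial's main conclusion with it, does not depend on this sentence.

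**What to change.** In the Statistical analysis section, replace the Wilcoxon rank sum test with the Wilcoxon signed-rank test for before-after comparisons within each arm. A paired t test with a 95% CI for the mean change would also do. The cost is one sentence. The design, sample size, data collection and between-arm analysis stay as they are.

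### The before-after comparison is assigned the Wilcoxon rank sum test, which ignores the pairing within patients; under the positive correlation to be expected it is conservative and loses power.

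*Protocol article*

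**What the plan says.** The Statistical analysis section gives each kind of comparison its own test. For continuous outcomes between arms: "Group differences for continuous variables will be analyzed using analysis of variance (ANOVA) to compare the subjective and semi-objective outcomes". The next sentence reads: "The Wilcoxon rank sum test will be used to compare the outcome measurements before and after treatment". Categorical variables and adverse effects then go to the chi-square test. One threshold covers everything: a P "value of 0.05 or less will be considered significant".

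The outcome sections show that the same patients are measured repeatedly. For the SF-36: "This survey will be performed before treatment, after the 5th and 10th treatments and at the end of the follow-up period". For pain threshold: "PT will be assessed before and after treatment and the mean value calculated after the 5th and 10th treatments". The pain diary likewise covers baseline, the 5th and 10th treatments, and the end of follow-up. The article names no paired test.

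**The concern.** The rank sum (Mann-Whitney) test derives its null variance on the premise that the two sets of values are unrelated. Two measurements on one patient are normally positively correlated, so the variance of their difference is smaller than the test assumes. The statistic is then divided by too large a standard error. The P value comes out too large, and a genuine change within an arm can be reported as not significant. The Wilcoxon signed-rank test has a similar name but works on within-patient differences, which is what this comparison needs.

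At stake is the correctness of the within-arm results, chiefly for the secondary outcomes. An analyst who follows the text literally would run the wrong procedure.

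**Working it through.** **Which comparison the sentence governs.** The sentence before it gives group differences in continuous outcomes to ANOVA, and the sentence after it gives categorical differences to chi-square. What remains is the comparison of patients with themselves. A between-group reading is strained, because the rank sum test compares two samples and the trial has five arms.

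**Inputs from the protocol.** The level is 0.05; its sidedness is not stated, so two-sided is assumed. The number per arm is "a minimum sample size of 30 individuals in each group" evaluable and 35 recruited ("With a maximum allowable dropout rate of 15%, a total of 175 subjects (35 per group) are being recruited").

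**Inputs assumed.** The document gives neither the before-after correlation (rho) nor an effect size for any secondary outcome. Rho is varied over 0, 0.3, 0.5 and 0.7. The shift for the power check is 0.5 SD of the raw score. Scores are taken as bivariate normal.

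**True level, by formula.** Leaving out the covariance overstates the variance of the difference by a factor of about 1/(1 − rho). The true two-sided level is then approximately 2 × [1 − Phi(1.96 / sqrt(1 − rho))]:

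- rho 0: 1.96 / 1 = 1.96, giving 5.0%
- rho 0.3: 1.96 / 0.837 = 2.34, giving 1.9%
- rho 0.5: 1.96 / 0.707 = 2.77, giving 0.6%
- rho 0.7: 1.96 / 0.548 = 3.58, giving 0.03%

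**True level, by simulation** (20,000 runs per setting, no true change):

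| rho | Rank sum, n = 30 | Rank sum, n = 35 | Signed-rank, n = 30 | Signed-rank, n = 35 |
|---|---|---|---|---|
| 0 | 4.6% | 4.8% | 4.8% | 5.0% |
| 0.3 | 2.2% | 2.1% | 5.3% | 5.0% |
| 0.5 | 0.6% | 0.9% | 4.7% | 4.7% |
| 0.7 | 0.06% | 0.08% | 4.8% | 4.7% |

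A repeat with 50,000 runs gave rank sum levels of 2.1%, 0.7% and 0.11% at n = 30, and 2.0%, 0.7% and 0.11% at n = 35, for rho 0.3, 0.5 and 0.7. The plan's nominal 5% is therefore reproduced only when rho is 0. The signed-rank test holds it throughout.

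**Power for a raw shift of 0.5 SD, n = 30:**

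| rho | Rank sum | Signed-rank |
|---|---|---|
| 0.3 | 44% | 59% |
| 0.5 | 44% | 74% |
| 0.7 | 43% | 91% |

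At n = 35 the pairs are 52% and 66%, 53% and 80%, and 55% and 95%.

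**The primary outcome.** The sample size section takes as expected values "mean changes in NPQ were 20.71 ± 11.91 (acupuncture group) and 24.04 ± 11.83 (control group"). The smaller change is 20.71 / 11.91 = 1.74 SDs of the change. In raw-score SDs this is 1.74 × sqrt(2 × (1 − rho)), or 2.06, 1.74 and 1.35 at rho 0.3, 0.5 and 0.7. With 30 patients, both tests rejected in every one of 10,000 simulated trials at each of these correlations. Even at rho 0.9 the rank sum test rejected in 99%. The choice of test hardly matters for a before-after change of that size.

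**The case against.** The strongest reply is that little depends on this sentence. The trial's aims are between-group: traditional against sham acupuncture, and which sham is the best control. Those comparisons go to ANOVA, so the efficacy comparison is not affected. The expected NPQ change is so large that the named test would detect it anyway. The sentence may also be no more than a slip between two similarly named tests. All of this stands and limits the importance of the point, but it does not make the named test right. The article assigns a specific test to a specific comparison, so this is not a detail left to a fuller document.

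Three stronger readings are tempting, and the documents do not support them.

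- **Too many false positives.** A reader might infer this from the statement that the error rate is wrong. With positive correlation the reverse is true: the level falls below 5%. Only a negative within-patient correlation would inflate it.
- **A bias in the choice of sham.** A reader might infer that missed within-arm changes would make an active sham look inert. No section says that within-arm P values will decide which sham is inert or optimal. Even a correct paired test would mix the effect of needling with natural course and regression to the mean.
- **A steeper loss of power.** If the effect is fixed at 0.49 SD of the difference, rank sum power at n = 35 falls to 66%, 51% and 24% at rho 0.3, 0.5 and 0.7, against 78% for signed-rank. Part of that fall is built in, because the raw shift, 0.49 × sqrt(2 × (1 − rho)), shrinks from 0.58 to 0.49 to 0.38 SD. With a fixed raw shift, rank sum power is flat and signed-rank power rises, as tabulated above.

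**Conclusion.** The point holds as an error in the named test, with a limited consequence. At plausible positive correlations the test runs at about 2% to 0.1% or less instead of 5%. For a moderate change it gives up roughly 15 to 48 percentage points of power at n = 30 (59 − 44 = 15; 91 − 43 = 48). Real within-arm changes in the secondary outcomes may be missed; the document does not allow the stronger statement that they will be. The sizes rest on assumed correlations, an assumed 0.5 SD shift, normal scores and a two-sided level. The direction needs only that a patient's before and after values are positively correlated.

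**What to change.** In the Statistical analysis section, replace the rank sum test with the Wilcoxon signed-rank test for before-after comparisons within an arm. Alternatively, report the mean paired change with its 95% confidence interval. Keep the rank sum test, if it is wanted at all, for comparisons between two arms. Label the within-arm analysis as supportive, and add that it does not by itself show whether a sham is inert.

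The cost is one phrase and one sentence of text. Design, sample size and data collection are unchanged, and the named software offers both tests.
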